#### Community members

The community members will participate at the three phases of the study.

For the base- and endline surveys, participants will be consenting residents of the community aged ≥18 years. A resident will be someone who has been living in the community for 6 months or more. Those who are sick at time of survey, mentally challenged or have communication challenge and pregnant women will be excluded from the survey. In addition, at endline survey, a subgroup of participants in the intervention arm will be randomly selected to participate in focus group discussions and in-depth interviews to explore their acceptability and perception of quality of the CORPs delivered follow-up care, as well as perceived challenges to implementation and sustainability.

For recruitment into the intervention, those found at community screening to have elevated blood pressure and same confirmed in the health facility, old patients receiving treatment and not controlled or not on treatment will be eligible for recruitment. They must plan to reside in the community for at least 1 year after enrollment and willing to participate in the home-based follow-up care by CORPs. To be excluded are patients with clinically established complications and other cardiovascular diseases, patients needing or on special medical services and pregnant women. The health workers to recruit at the health facilities will be medical officers of health and nurses involved in the care of adults in the health facilities. They will be trained on diagnosis, treatment and prevention of hypertension as well as use of the national guideline for treatment of hypertension.

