## Statistical methods

### Statistical methods for primary and secondary outcomes {20a}

Data analysis will be carried out using Stata MP version 14 based on the CONSORT 2010 guideline [40]. Intention-to-treat analysis will be applied. Continuous variable will be presented as mean and standard deviations (SDs) or medians with their 25th and 75th percentiles when the distribution of the data does not follow a Gaussian distribution. Categorical variables shall be presented as frequencies and percentages.

Baseline characteristics of participants in the intervention and control arms will be compared to assess balance and identify any variable that need to be adjusted in the final analysis. The primary outcome is achievement of blood pressure control at 6 months post-intervention. The effect of intervention within each of the study groups will be carried out comparing baseline and 6 months post-intervention using McNemar test. Depending on the distribution of baseline characteristics, random effect logit model will be fitted to estimate treatment effect size comparing the two groups. Similar analysis will be done for categorical secondary outcomes such as treatment adherence.

Cost-effectiveness analysis will also be carried out using the ingredient approach [41].

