### Methods for additional analyses (e.g. subgroup analyses) {20b}

Numerical secondary outcomes such as mean change in systolic blood pressure will be analysed using two approaches. First, a difference-in-difference method [42] would be employed to compare mean SBP between baseline and 6-month post-intervention. This will be an assessment of within-group changes in blood pressure. Secondly, a linear mixed model will be implemented to determine the treatment effect as a measure of between-group comparison of intervention and control arms.

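### For blood pressure control at 6 months, the intervention effect is assessed by McNemar tests within each arm, and the only between-arm model named for it is worded as depending on baseline balance

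*Protocol article*

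**What the plan says.** All places are in the protocol article.

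- **Statistical methods for primary and secondary outcomes {20a}** names the endpoint: "The primary outcome is achievement of blood pressure control at 6 months post-intervention". It then says: "The effect of intervention within each of the study groups will be carried out comparing baseline and 6 months post-intervention using McNemar test". The between-arm comparison follows: "Depending on the distribution of baseline characteristics, random effect logit model will be fitted to estimate treatment effect size comparing the two groups". Categorical secondary outcomes are to be handled in a similar way.
- The same section says the arms' baseline characteristics will be "compared to assess balance and identify any variable that need to be adjusted in the final analysis".
- **Methods for additional analyses {20b}** says that "a difference-in-difference method [42] would be employed to compare mean SBP between baseline and 6-month post-intervention", and describes this step as follows: "This will be an assessment of within-group changes in blood pressure". As a second approach, "a linear mixed model will be implemented to determine the treatment effect as a measure of between-group comparison of intervention and control arms". No condition is attached to that model.
- **Eligibility criteria {10}, Community members** admits people whose raised pressure at screening is confirmed at the facility, and says that "old patients receiving treatment and not controlled or not on treatment will be eligible for recruitment".

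**The concern.** A before-after test in one arm cannot separate the intervention from anything else that lowers pressure over six months. Two such forces are built into this design. Patients enter because their pressure is high, so regression to the mean is expected. Community screening and referral also take place in both arms (Table 1), so treatment may start in both. In the control arm there is no intervention whose effect the test could measure. McNemar also treats patients as independent, although communities are the randomised units.

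The comparison that does answer the question is the random-effect logit. As worded, whether it is fitted turns on what the baseline data look like. If the condition governs only adjustment, the covariates of the primary model are still chosen by looking for imbalance. Under random allocation, observed imbalance is a poor guide to which covariates matter, and choosing the model this way makes the primary p-value depend on an unspecified data-driven step.

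At stake is a report of significant improvement in the intervention arm, offered in support of scale-up, when the arms do not differ.

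**Working it through.** The plan gives no figure of its own on this point. Its sample size enters only as counts.

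**Inputs**
- 50 patients per arm in each LGA and 10% attrition (Sample size {14}): 50 × 0.9 = 45 completers.
- 600 patients in total, 300 per arm over six LGAs: 300 × 0.9 = 270 completers.
- Two-sided 5% level.
- Baseline control taken as 0%, from the eligibility rule, with the same entry rule assumed in both arms.
- Probability c of becoming controlled by 6 months, equal in both arms: 5% to 30%. This is an assumption. The 30% in the sample size section is the proportion of people living with hypertension who are controlled, not a conversion rate from zero, and it serves here only as the top of the range.

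**Step 1: the McNemar threshold.** With k discordant pairs, all improvements, the exact two-sided p is 2 × 0.5^k.
- k = 5: 2 × 0.03125 = 0.0625.
- k = 6: 2 × 0.015625 = 0.031.

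Six conversions are enough, whether the arm has 45 or 270 patients.

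**Step 2: chance of significance with no difference between arms.** One arm: a = P(Bin(n, c) ≥ 6). Both arms: a². Exactly one arm: 2a(1 − a).

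| n per arm | c | one arm (a) | both arms | exactly one |
|---|---|---|---|---|
| 45 | 5% | 0.024 | 0.001 | 0.047 |
| 45 | 10% | 0.292 | 0.085 | 0.414 |
| 45 | 20% | 0.910 | 0.828 | 0.164 |
| 45 | 30% | 0.997 | 0.995 | 0.005 |
| 270 | 5% | 0.993 | 0.987 | 0.013 |
| 270 | 10% to 30% | 1.00 | 1.00 | 0.00 |

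A simulation of 20,000 trials agrees (for example 0.996 for both arms at n = 45, c = 30%). In the same runs a simple between-arm test of proportions rejected in 0.045 to 0.060 of trials, close to its nominal 5%. Neither calculation includes clustering.

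**Step 3: if baseline control were not zero.** Take 30% controlled at baseline, 30% of the uncontrolled gaining control and 20% of the controlled losing it: 0.3 × 0.8 + 0.7 × 0.3 = 0.45 at 6 months in both arms. By simulation, both McNemar tests are significant with probability 0.15 at 45 per arm and 0.997 at 270. At the full sample size the conclusion does not rest on the 0% assumption.

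**Step 4: difference-in-difference.** The estimator is (intervention mean at 6 months − intervention mean at baseline) − (control mean at 6 months − control mean at baseline). It needs both arms and contrasts their changes. A within-arm change is only one of the two brackets. The method named in {20b} and the description attached to it cannot both be followed. Outcomes {12} states the mean blood pressure outcome as a contrast between intervention and control communities, which fits the estimator and not the label.

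**The case against.** Section {20a} speaks of McNemar as operating within groups and keeps treatment effect size for the logit, so it never says that a within-arm p-value will be read as effectiveness. Significance in both arms would in fact warn a careful reader against crediting the intervention. The conditional phrase comes shortly after a sentence on choosing adjustment variables, so it may govern adjustment only. The Discussion also mentions multilevel random-effect analysis for urban and rural differences, without a condition.

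Much of this stands. The adjustment-only reading is plausible, but it leaves covariates picked from observed imbalance, which is a stated rule and not a detail left to an analysis plan. The Discussion sentence names neither the outcome nor the arm comparison. On interpretation, the McNemar sentence does use the words for an intervention effect. Significance in one arm only is the more misleading pattern, and it is not always rare: at 45 per arm and 10% conversion it occurs with probability 0.414, and by symmetry half of that (0.207) favours the intervention arm. At 270 per arm it is at most 0.013 over the range shown.

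A reader might also infer several stronger points that the documents do not support:
- *That the whole trial lacks an unconditional between-arm analysis.* It does not: the linear mixed model for systolic pressure carries no condition.
- *That both McNemar tests will be significant whatever happens.* At 45 per arm and 10% conversion, both are significant only about 9% of the time. The figure of 45 is one arm of one LGA, and no analysis by LGA is described.
- *That the logit is the only valid analysis.* With two groups of communities in each of six LGAs (12 allocated groups), a cluster-level analysis is a recognised alternative.
- *That the mixed model is inefficient.* The protocol does not say that it uses change scores, so no loss of precision can be shown.

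**Conclusion.** The point holds for blood pressure control at 6 months and, through the similar-analysis sentence, for the categorical secondary outcomes. The within-arm McNemar tests are not evidence of an intervention effect. At the full sample size, both would be significant with probability 0.99 to 1.00 under equal conversion of 5% to 30% in the two arms. At 45 per arm the range is 0.001 to 0.995, so the smaller figure depends heavily on the assumed rate. These results rest on near-zero baseline control, the same entry rule in both arms, independent patients and conversion rates that the documents do not give.

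The between-arm logit is at best adjusted by a data-driven rule and at worst fitted only under an unstated condition. The difference-in-difference label is a plain misdescription. The linear mixed model for systolic pressure is not at fault. Because the wording governs inference on the primary outcome, it should be corrected before outcome data exist.

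**What to change.** - **Primary outcome.** State the between-arm random-effect logit on 6-month control as the primary analysis, with no condition. Adjust for a fixed set named in advance that includes baseline systolic pressure and LGA, the level within which communities are allocated. Keep the baseline table for description and do not select covariates from it.
- **Within-arm change.** Report it descriptively in each arm. Do not present McNemar p-values as evidence of effect.
- **Categorical secondary outcomes.** Apply the same unconditional between-arm rule.
- **Systolic pressure.** Name the linear mixed model, with baseline systolic pressure as a covariate, as the main analysis. If difference-in-difference is kept, define it as the arm-by-time contrast and label it a sensitivity analysis.

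The cost is analysis wording only. Blood pressure at baseline and 6 months and LGA are already part of the design, and the Trial status section says recruitment to the intervention had not begun.

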#### Qualitative data

The audiotape recordings from the FGD and KIIs will be transcribed verbatim and translated into English. This will be analysed by content analysis using NVIVO. The text will be entered into NVIVO and codes and themes on acceptability and performance of the CORPs and quality of the intervention will be generated.

Qualitative data analysis of qualitative data from the FGDs will be done using Nvivo 9® software and manual coding. The audio recordings from FGDs will be transcribed verbatim and translated into English. Caution will be taken to ensure that no data will be lost during translation. The text data will be entered into Nvivo 9® software and analysed for themes on perceptions about quality and acceptability of the CHW intervention in the community

### Interim analyses {21b}

Interim analysis will not be carried out.

### Methods for additional analyses (e.g. subgroup analyses) {20b}

Numerical secondary outcomes such as mean change in systolic blood pressure will be analysed using two approaches. First, a difference-in-difference method [42] would be employed to compare mean SBP between baseline and 6-month post-intervention. This will be an assessment of within-group changes in blood pressure. Secondly, a linear mixed model will be implemented to determine the treatment effect as a measure of between-group comparison of intervention and control arms.

### Methods in analysis to handle protocol non-adherence and any statistical methods to handle missing data {20c}

The use of CORPS who are based in the study communities and monthly home visit will help to minimize the occurrence of missing data and losses to follow-up. During analysis, sensitivity analyses will be carried out to assess the patterns of missing data and loss-to-follow-up so that appropriate decisions can be taken on whether multiple imputation methods need to be employed. The level of significance will be set at 5%.

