**Methods:**

An intervention study will be conducted in three states using a mixed method design. First is a baseline survey using a semi-structured pre-tested questionnaire to collect information on demographics, clinical data, knowledge, occurrence and risk factors of hypertension among 1704 adults ≥18 years. Focus group discussions (FGD) and key informant interviews (KII) will be conducted to explore a community’s experience of hypertension, challenges with hypertension management and support required to improve control in 10 selected communities in each state. The second is a cluster-randomized controlled trial to evaluate effect of a package on reduction of blood pressure (BP) and prevention of cardiovascular (CVD) risk factors among 200 hypertensive patients to be followed up in intervention and control arms over a 6-month period in each state. The package will include trained CORPs conducting community-based screening of BP and referral, diagnosis confirmation and initial treatment in the health facility, followed by monthly home-based follow-up care and provision of health education on hypertension control and healthy lifestyle enhanced by phone voice message reminders. In the control arm, the usual care (diagnosis, treatment and follow-up care in hospital of a patient’s choice) will continue. Third, an endline survey will be conducted in both intervention and control communities to evaluate changes in mean BP, control, knowledge and proportion of other CVD risk factors. In addition, FGD and KII will be used to assess participants’ perceived quality and acceptability of the interventions as delivered by CORPs.

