### Intervention description {11a}

The highlights of the activities and assessments for intervention and control arm are shown in Table 1. The components of the intervention include the following.

**Table 1 Tab1:** Highlights of the activities and assessments for intervention and control arm

	Activity	Intervention	Control
1	Baseline survey	Yes	Yes
2	Selection, screening and standard training of CORPs on blood pressure screening	Yes	Yes
3	Training on additional information on follow-up care for hypertensive patients and CORPs coordination	Yes	No
4	Trained CORPs screen and refer community members found to have high blood pressure	Yes Referral to the designated primary healthcare centre in the community	Yes Referral will be to the community member’s health facility of choice
5	Train health facility staff in designated primary healthcare facilities on the National guideline for hypertension treatment	Yes	No
6	CORPs Monthly checking and recording of blood pressure as well as providing health education/counselling support by the CORPs	Yes	No
7	SMS messaging on medication and healthy lifestyle adherence to support follow-up care	Yes	No
8	Anthropometry measurement, e.g. weight, height and body mass index (BMI) Biochemical measurement ECG	Yes	No
9	Endline survey	Yes	Yes

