### Relevant concomitant care permitted or prohibited during the trial {11d}

This trial involves screening, diagnosis and treatment of hypertension. The control arm will be on the standard/usual care while the intervention will have in addition to standard care follow-up care at home by trained community-oriented resource person. This is an implementation research which will be carried out in a real-life situation. There will be no concomitant care and participants will be advised to take only medications prescribed in health facilities or report any other medication that may have been taken during the period in the trial.

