### Plans to promote participant retention and complete follow-up {18b}

Participants will be provided adequate information on the project and their role as well as what is expected of them emphasizing completeness of follow-up. It will be ascertained at time of recruitment that the participant will be resident in the community for at least a year. The participants will be linked to the CORPs in their community who will provide follow-up care and visit them to check on adherence to clinic follow-up visit. The participant is recruited from the catchment area of the clinic; hence, it is assumed that this will encourage clinic as distance to clinic will not be a barrier to follow-up visit. The proportion of participants who visit the clinic and those who had home follow-up visit by CORPs as scheduled shall be measured at the end of the 6-month follow-up visit.

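### The stated measures to limit missing data reach the intervention arm only, and imputation is decided after the missingness is seen, so outcome-related loss that differs by arm is a real, though unproven, risk

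*Protocol article*

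**What the plan says.** **Retention.** The missing-data section {20c} relies on CORPs and their home visits: "The use of CORPS who are based in the study communities and monthly home visit will help to minimize the occurrence of missing data". The retention section {18b} relies on the same people: "The participants will be linked to the CORPs in their community who will provide follow-up care and visit them". It also argues that patients live in the clinic's catchment area, so distance should not keep them away, and it adds general study information and a residence check at recruitment.

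**Who receives this.** Table 1, row 6 (Intervention description {11a}) lists "CORPs Monthly checking and recording of blood pressure as well as providing health education/counselling support by the CORPs" as Yes for intervention and No for control. The concomitant-care section {11d} agrees: "the intervention will have in addition to standard care follow-up care at home by trained community-oriented resource person". Row 7 gives the text messages to the intervention arm only, and the clinic appointment schedule in {11a} is written for intervention sites. For control patients, the abstract says "the usual care (diagnosis, treatment and follow-up care in hospital of a patient’s choice) will continue".

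**Analysis.** Section {20a} states "Intention-to-treat analysis will be applied". Section {20c} says that patterns of missing data and loss will be assessed during analysis "so that appropriate decisions can be taken on whether multiple imputation methods need to be employed".

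**Exit rule.** Section {11b} allows an intervention patient whose BP is not controlled over two CORP visits to be withdrawn from the study after review of the case. No such rule is given for control patients.

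**The concern.** The device meant to keep data complete is part of the treatment under test. A patient visited at home each month is easier to find at month 6 than one attending a facility of his or her own choice. The catchment-area argument does not cover control patients for the same reason. Randomising communities does not protect the contrast if completeness then differs by arm and is related to BP control.

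The imputation rule does not close the gap. Observed patterns can show that loss differs by arm or by baseline characteristics. They cannot show whether, given those, loss depends on the month-6 BP that was never measured, which is the feature that matters for bias. Leaving the choice until the data are in also lets the primary result depend on a decision made with those data in view.

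The withdrawal rule in {11b} is a route to loss that depends on the outcome and exists in one arm only. If withdrawn patients have no endline reading, the remaining intervention patients are selected for being controlled.

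**Working it through.** **Inputs from the protocol.** Proportion controlled without the intervention is 30%, and 60% is anticipated with it (Sample size {14}). Attrition is 10%, one figure. Monthly CORP follow-up is Yes / No by arm (Table 1, row 6). The endline survey is Yes / Yes (row 9).

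**The plan's own figure.** Attrition enters only the 50 per arm. From the stated inputs, (1.96 + 1.28)² × (0.30×0.70 + 0.60×0.40) / 0.30² = 52.5, so 53, and 53 / 0.90 = 58.9, so 59. The 50 does not reproduce. That is a separate matter and has no bearing on this point.

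**Assumed, because the protocol gives no loss by arm.** Loss in each arm; the proportion q controlled among those lost; no true effect, with 30% truly controlled in both arms; and a complete-case contrast.

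**Step 1: loss to follow-up.** Observed rate = (0.30 − loss × q) / (1 − loss).

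| Loss, intervention / control | q | Intervention | Control | Spurious difference |
|---|---|---|---|---|
| 5% / 20% | 0 | 0.30/0.95 = 31.6% | 0.30/0.80 = 37.5% | −5.9 points |
| 5% / 20% | 30% | 0.285/0.95 = 30.0% | 0.24/0.80 = 30.0% | 0 |
| 5% / 20% | 60% | 0.27/0.95 = 28.4% | 0.18/0.80 = 22.5% | +5.9 points |
| 5% / 15% | 10% | 31.1% | 33.5% | −2.5 points |
| 5% / 15% | 50% | 28.9% | 26.5% | +2.5 points |
| 5% / 25% | 10% | 31.1% | 36.7% | −5.6 points |
| 5% / 25% | 50% | 28.9% | 23.3% | +5.6 points |
| 10% / 10% | same in both arms | equal | equal | 0 |

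Unequal loss alone does no harm; bias needs q to differ from 30%. Equal loss is safe only if q is the same in both arms. At 10% / 10% with q = 10% in the intervention arm and 50% in control, the rates are 0.29/0.90 = 32.2% and 0.25/0.90 = 27.8%, a spurious +4.4 points.

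**Step 2: withdrawal of uncontrolled patients, intervention arm only.** If a fraction w of the arm is withdrawn, all uncontrolled, with no endline reading and no loss in control, the bias is 0.30/(1 − w) − 0.30.
- w = 10%: 33.3% − 30% = +3.3 points.
- w = 20%: 37.5% − 30% = +7.5 points.

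**Step 3: would counting missing as not controlled settle it?** At 5% / 20% loss:
- q = 0: 30% and 30%, difference 0.
- q = 30%: 0.30 − 0.05×0.30 = 28.5% and 0.30 − 0.20×0.30 = 24.0%, a spurious +4.5 points.
- q = 60%: 27% and 18%, a spurious +9 points, which is worse than the complete-case +5.9.

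That rule is correct at only one end of the range, so it cannot serve as a check on its own.

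**The case against.** The strongest reply is that a reader might infer that unequal loss is built in and left unhandled, and the protocol does not support that. The endline survey covers both arms. CORPs are trained and screen in control communities too (Table 1, rows 2 and 4). The residence check is not arm-specific. Intention to treat, a random-effect logit model, a linear mixed model, a review of missingness patterns and optional multiple imputation are all stated. This stands: what is built in is unequal effort, not unequal loss.

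Two further inferences also fail. One is that interim BP exists only in the intervention arm. Outcomes {12} says the outcome variables are measured at months 2, 4 and 6 without restricting this to an arm, although no control-arm procedure for months 2 and 4 is described. The other is that a single 10% attrition figure contradicts the design. It is a planning allowance and does not assert equal loss.

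It is also fair to say that the imputation model and its assumptions belong in an analysis plan that is not shown, so their absence is no fault. What remains is a rule the protocol does state: whether to impute is settled during analysis from observed patterns. Intention to treat and random-effect or mixed models do not answer this, since none of them recovers an outcome whose absence depends on its own unseen value.

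Finally, the loss rates above are assumptions. They show how large the bias could be, not that this trial will have it.

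**Conclusion.** The point holds in limited form. The named measures against missing data act in the intervention arm, nothing equivalent is named for control patients, and the imputation decision is tied to patterns that cannot answer the relevant question. Differential, outcome-related loss is therefore a real risk that the protocol does not establish as fact.

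On assumed losses of 5% and 20%, a complete-case contrast would be off by between −5.9 and +5.9 points, and by 0 if those lost have the same 30% control rate. The outer figure is about a fifth of the planned 30-point difference (5.9/30). It would not manufacture the anticipated effect but could distort a smaller one, and its direction cannot be told in advance. The withdrawal rule in {11b} is different: if withdrawn patients are not measured at endline, it pushes towards the intervention, by +3.3 points at 10% withdrawn and +7.5 at 20%. Sections {11b} and {20a} must be reconciled on whether withdrawn patients stay in the analysis and are still measured; nothing is implied here about the clinical rule itself.

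**What to change.** 1. **Equal tracing.** Use the CORPs already trained in control communities for contact-detail checks only, with no BP reading and no counselling, on the same tracing schedule in both arms. Make the same endline BP attempt for every enrolled patient, including those withdrawn under {11b}, so that {11b} and intention to treat agree on data collection.
2. **Method fixed in advance.** Replace the decide-by-pattern wording in {20c} with a primary missing-data method fixed before outcome data are seen. It should use baseline BP and any BP readings available, including months 2 and 4 if they are collected in both arms as Outcomes {12} implies. State whether they are.
3. **Two-arm tipping point.** Add a sensitivity analysis that varies the missing outcomes in both arms, including withdrawn intervention patients. Treat missing as not controlled as one point in that range, not as a stand-alone check.

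**Cost.** Items 2 and 3 are wording and analyst time. Item 1 is a small change to field procedure that takes some CORP and interviewer time; its downside is brief extra contact in a usual-care arm. Trial status says recruitment to the intervention had not started, so on the document's own account the change could be made before enrolment.
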